All patients identified will receive a letter of invitation by mail informing them about the research project and inviting them to participate in the study. Two weeks after the invitation, the study team will contact the candidates by phone and explain the study protocol in detail, answer their questions and formally invite them to participate.

If the candidate agrees to participate in the study, a face-to-face interview will be scheduled. During this interview the investigators will explain the study design and intervention to the candidate, and if the candidate agrees to participate in the study, he/she will be asked to sign the informed consent form. Subjects will then be screened for inclusion/exclusion criteria and determined to be eligible or not for the study at that point. (Please refer to section d: Study timeline for details)

*We will also post the study on ClinicalTrials.gov website.*

- 1. Inclusion and Exclusion Criteria

Inclusion criteria:

- Age > 18 years.
- Patients with ESRD on PD.
- Patients are able to understand and give consent.
- Patients with estimated daily dietary AGE intake > 12 AGE Eq/day (12,000 kiloUnits/day) based on 3-day food records.

Exclusion criteria:

- History of diabetes mellitus.
- Patient on antibiotics in the last three months.
- Liver cirrhosis, and heart failure with EF < 30%.
- The use of chemotherapy, immunosuppressive medications, probiotics, and steroid in the last month.
- Oral iron supplementation in the last month.
- History of small or large intestine resection or small bowel obstruction.
  1. Number of Subjects

A minimum of 30 participants (15 in each group) is required. Based on previous experience, we expect a 20% drop out and extrapolate that an initial enrollment of 30 participants (15 in each group) will be sufficient to achieve at least 10 participants in each group at study end.

This is a pilot study. There are no prior studies evaluating the effects of dietary AGEs on gut microbiota in normal subjects or patients with different disease including kidney diseases. Thus the investigators cannot perform power analysis and sample size calculation. Based on our prior experience and recruitment rate and drop off noted when conducting a similar study we believe that 20 patients divided in two groups is a feasible and obtainable sample size.

Subjects will be divided in two groups:

- G1: 15 patients will continue their original diet.
- G2: 15 patients will be instructed to initiate a low AGE diet.

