**Step 2: first visit:**

Enrollment: At this point, candidates are officially enrolled in the study. . Patients on PD are seen by their primary nephrologist every month and blood tests are obtained monthly to evaluate dialysis efficacy and other parameters in this population (standard treatment for ESRD patients on PD).

The first visit will be scheduled to take place during one of the regular monthly dialysis visit, and the study blood samples will be obtained in addition to the blood samples obtained in the regular monthly visit.

Medical evaluation: This will take place during the PD monthly visit. Vital sign measurements and physical examination will be conducted as part of the standard of care, and reviewed by the investigators.

Diet evaluation: Candidates will bring detailed, accurate 3 day diet log for the nutritionist to evaluate.

Sample collection: Stool sample will be obtained and immediately stored in -80C at Annenberg building, floor 23 [name] lab. A total of 45 ml (three tablespoons) will be obtained during this visit. 15 ml (one tablespoon) will be sent to the hospital laboratory to evaluate dialysis parameters as the standard of care. An extra blood sample [30 ml (two tablespoons)] will be obtained for the research study. Blood will be centrifuged to separate supernatant and mononuclear cells and both fractions will be immediately stored in -80C at Annenberg building, floor 23 ([name] lab). 24 hour urine samples will be obtained during this meeting and immediately stored at -80C at Annenberg building, floor 23 [name] lab (see paragraph f for details). Candidates will be given another set of sample collection tools (disposable: two ice packs, a box, two tubes, and urine collection container) to bring in the second visit.

Skin AGE measurement: Measurement of AGE levels in the skin will be done using an AGE reader. This AGE reader provides a non-invasive cardiovascular risk assessment by illuminating the skin of the forearm. The skin AGEs will emit a light that is detected by the AGE reader. The test will last about 10 seconds.

Randomization: Candidates will be randomly assigned to either continue the same diet [G1], or switch to low AGE diet [G2].

Diet education (30 minutes): The study dietitian will meet with both groups and instruct them in regards to food preparation and its content of AGE. Handouts will be given to both groups (see attached).

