**Step 4: final evaluation:**

Visit: This visit will take place one month after the first visit (enrollment and randomization visit). This visit will be scheduled to take place during the regular monthly dialysis visit, and the study blood samples will be obtained in addition to the blood samples obtained in the regular monthly visit

Diet evaluation: Candidates will bring detailed, accurate 3 days diet log for the nutritionist to evaluate.

Sample collection: Stool sample will be obtained and immediately stored in -80C at Annenberg building, floor 23 [name] lab. A total of 45 ml (three tablespoons) will be obtained during this visit. 15 ml (one tablespoon) will be sent to the hospital laboratory to evaluate dialysis parameters as the standard of care. An extra blood sample [30 ml (two tablespoons)] will be obtained for the research study. Blood will be centrifuged to separate supernatant and mononuclear cells and both fractions will be immediately stored in -80C at Annenberg building, floor 23 [name] lab. 24 hour urine samples will be obtained during this meeting and immediately stored in -80C at Annenberg building, floor 23 [name] lab.

Skin AGE measurement: Measurement of AGE levels in the skin will be done using an AGE reader. This AGE reader provides a non-invasive cardiovascular risk assessment by illuminating the skin of the forearm. The skin AGEs will emit a light that is detected by the AGE reader. The test will last about 10 seconds.

The expected duration of enrollment is **1** year.

The estimated date for the investigators to complete this study is 12/31/2016

- 1. Study Endpoints

Primary Endpoint: Change of gut microbiota after intervention.

Secondary Endpoint: Inflammatory and metabolic marker changes after intervention.

Safety endpoint: Candidates will be asked to either continue with their regular diet, or asked to cook their food in a different way, mainly boiling instead of frying/grilling. All cooking methods and measures to decrease AGE in diet are considered universally safe and are routinely recommended to the general population regardless of their medical conditions.

- 1. Procedures Involved in the Human Research

An initial phone interview will be conducted to invite potential study candidates to participate.

Face-to-face interviews will be performed to obtain consent and medical history as well as and provide training on recording dietary log. Stool, urine and blood samples will be obtained during both meetings.

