Metabolon Inc. Durham NC. (Company responsible of metabolite analysis) will receive specimens labeled with the letter code. No protected health information will be submitted with the specimens. Regulatory agency will be permitted access the results of these analyses upon request. All requests will have to be approved by the study principle investigator.

Stool samples for microbiota study will be handled by [name] lab.

- 1. Data Management and Confidentiality

Names and dates of birth will be stored in a file, and each patient will be assigned a letter code. Data collected will be stored in a separate file, using the assigned letter code as the identifier. Both files will be stored in a computerized database with a secure access and password available only to the investigators.

After initial processing of samples, a small portion of serum, stool and urine will be sent completely de-identified to Metabolon Inc. Durham NC. for metabolite analysis.

The results of their serum samples or urine samples will not be shared with the patients. No subject identifiers will be shared with Metabolon Inc. All data used in this study will be de-identified before being transferred to any person, organization, or database outside of Mount Sinai Medical Center. All patients will only be identified by the letter code (As mentioned above) on all study related materials in patient research folders and on the database. The log linking ID numbers to patient identities will be kept in a password protected and encrypted file on a Mount Sinai networked computer. The data will be kept for at least 2 years after the completion of the study. When transmitting data, only de- identified data will be used. All identifiable patient information will be stored on Mount Sinai’s protected server. All paper copies of forms and patient health information will be stored in a locked room at Mount Sinai Hospital.

Data will be analyzed using SPSS statistical program, for categorical values chi-square test will be used, for non categorical values analysis of variance (ANOVA) will be used.

Gut microbiota will be analyzed by sequencing of V4 region of 16S rRNA. Sequencing data will be analyzed using Qiime program ([name] lab).

- 1. Provisions to Monitor the Data to Ensure the Safety of subjects

**Part I** describes the safety monitoring activities that will be undertaken in during the study. This should be completed for all studies that require more than the basic minimum DSMP.

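### ANOVA is fixed for continuous outcomes with no baseline covariate and no stated dependent variable; ANCOVA on the pre-randomisation value would usually be more precise for scalar outcomes

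*Protocol*

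**What the plan says.** Under Data Management and Confidentiality, the protocol assigns the chi-square test to categorical data and states that "for non categorical values analysis of variance (ANOVA) will be used", in SPSS. No covariate is named, and the quantity to be analysed is not identified. The same section adds for the microbiota that "Sequencing data will be analyzed using Qiime program", without naming a test or a metric.

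Study Endpoints words both endpoints as changes: "Primary Endpoint: Change of gut microbiota after intervention" and "Secondary Endpoint: Inflammatory and metabolic marker changes after intervention".

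The first-visit description lists stool, blood, 24-hour urine and skin AGE measurement ahead of the allocation step, where "Candidates will be randomly assigned to either continue the same diet [G1], or switch to low AGE diet [G2". The final evaluation repeats the same measurements one month later. Procedures Involved in the Human Research confirms that "Stool, urine and blood samples will be obtained during both meetings".

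Number of Subjects says "A minimum of 30 participants (15 in each group) is required", expects 20% dropout and aims for at least 10 per group at the end. It states that no power calculation could be done.

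**The concern.** This is a two-arm randomised pre/post design, and each participant's own pre-randomisation value is available for the stool, serum, urine and skin measures. The natural comparison is the one-month value between groups, adjusted for that baseline. The stated method has no such adjustment and can be read in two ways:

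- ANOVA of the one-month value does not use baseline.
- ANOVA of the change subtracts baseline with a fixed coefficient of 1, which is too much whenever the pre-post correlation is below 1 (with equal SDs at both visits).

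Which reading performs better depends on a correlation that the protocol does not know. Leaving the form open also lets it be chosen after the data are seen. At stake is precision in a trial expected to finish with 10 to 12 per arm, where the estimated difference and its confidence interval are the main product of a pilot.

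**Working it through.** **Inputs from the protocol.** 15 per group enrolled; 20% dropout; target of at least 10 per group.

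**Inputs assumed, because the protocol gives none.** Two-sided alpha 0.05; true group difference of 1 SD; equal SD at both visits; linear baseline relation with a common slope; pre-post correlation rho from 0 to 0.9.

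**The plan's own figure.** 15 × (1 − 0.20) = 12 completers per arm, which meets the stated target of at least 10. There is no power figure to reproduce.

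**Variance of the group difference, relative to final-value ANOVA (= 1).**

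- Change-score ANOVA: 2(1 − rho). With two groups and two visits, the group-by-time test of a repeated-measures ANOVA is the same test.
- ANCOVA: (1 − rho²) × (1 + 1/(N − 4)). The second factor is the cost of estimating the slope. At N = 24 it is 1 + 1/20 = 1.05; at N = 20 it is 1 + 1/16 = 1.0625.

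Example at rho = 0.5, 12 per arm: change 2 × 0.5 = 1.00; ANCOVA 0.75 × 1.05 = 0.79. Equivalent size: 1/0.7875 = 1.27, a trial about 27% larger.

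**Power.** Noncentral t with noncentrality 1/√(V × 2/12), where V is the relative variance, on 22 df for ANOVA and 21 df for ANCOVA.

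| rho | V change | V ANCOVA | ANCOVA ÷ change | Power final | Power change | Power ANCOVA |
|---|---|---|---|---|---|---|
| 0 | 2.00 | 1.05 | 0.53 | 65% | 38% | 63% |
| 0.2 | 1.60 | 1.01 | 0.63 | 65% | 46% | 64% |
| 0.3 | 1.40 | 0.96 | 0.68 | 65% | 51% | 67% |
| 0.5 | 1.00 | 0.79 | 0.79 | 65% | 65% | 75% |
| 0.7 | 0.60 | 0.54 | 0.89 | 65% | 86% | 89% |
| 0.8 | 0.40 | 0.38 | 0.95 | 65% | 96% | 97% |
| 0.9 | 0.20 | 0.20 | 1.00 | 65% | 100% | 100% |

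**Break-even points at 12 per arm.** Against final values: 1.05(1 − rho²) = 1 gives rho² = 0.048, so rho is about 0.22. Against change scores: 1.05(1 + rho) = 2 gives rho of about 0.90.

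**At 10 per arm, rho = 0.5.** V ANCOVA is 0.75 × 1.0625 = 0.80; power is 56% for either ANOVA and 66% for ANCOVA.

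**Check by simulation** (20,000 runs, 12 per arm, rho = 0.5). Variance of the estimated difference was 0.165 for final values, 0.165 for change and 0.130 for ANCOVA; power was 0.655, 0.654 and 0.754. This agrees with the formulas.

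**The case against.** The strongest reply is that both endpoints are worded as changes, so baseline probably enters already. This stands in part. A reader might infer that the plan throws the baseline away, and the documents do not support that: the analysis sentence leaves the form open, and the endpoint wording favours change scores. Against change scores the gain at rho 0.7 is only about three power points (89% against 86%), and by 0.9 it is nil.

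A second reply is that model form and covariates belong in a SAP, which is not shown. But the protocol does not stay silent; it names a method for all non-categorical data. A more efficient method that uses data already collected is a fair comment on that choice.

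Four stronger readings should not be drawn:

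- That a repeated-measures ANOVA would estimate half the effect. This holds only for the group main effect, which the protocol never names as its test. The group-by-time test has no such problem.
- That ANCOVA would serve every continuous outcome. Microbiota composition is multivariate and goes to QIIME; a model with a single baseline covariate suits only scalar summaries.
- That the improvement is free. It costs one degree of freedom and 5 to 6% of variance.
- That the inflammatory markers or uremic toxins are skewed. The protocol gives no distributions, so transformation can only be conditional on the data.

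**Conclusion.** The point holds as one of efficiency. Both forms of ANOVA are unbiased under randomisation, and the pilot makes no power claim that could be undermined, so validity is not in question.

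The size depends on correlations that the protocol does not give. At 12 per arm and rho between 0.3 and 0.7, ANCOVA lowers variance by about 4 to 46% against final values and by about 32 to 11% against change scores.

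The unknown correlation argues for ANCOVA, because each ANOVA does badly where the other does well. Final-value analysis has 1/0.54, or about 1.9 times, the variance of ANCOVA at rho 0.7. Change-score analysis has 2.00/1.05, also about 1.9 times, at rho 0. ANCOVA's worst loss over the range at 12 per arm is about 5%, against final values at rho 0. With many markers that may differ in correlation, one rule that is best or nearly best throughout is preferable. The change should be made, but the trial does not stand or fall on it.

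**What to change.** Replace the ANOVA clause with text to this effect:

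*Scalar continuous outcomes (serum, urine and skin markers, and any scalar microbiota summary such as a diversity index) will be compared at one month by ANCOVA, with group as factor and the participant's own baseline value as covariate. Outcomes will be transformed where the observed distribution requires it. The adjusted G2 minus G1 difference will be reported with its 95% confidence interval. Multivariate microbiota composition will be analysed separately in QIIME.*

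This settles which quantity is analysed and uses only planned measurements. ANCOVA can be run in SPSS, the package already named. The price is one degree of freedom and about 5% (12 per arm) to 6% (10 per arm) of variance for the estimated slope. The baseline relation must be roughly linear, possibly after transformation.

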**Part I: Elements of a Data and Safety Monitoring Plan**

1. List the name(s) of the individual(s) at MSSM who will be responsible for data and safety monitoring of this study. For each individual, indicate their role, name, title, and department information. The Principal Investigator may be the only monitor of a study.

If the qualifications of an individual to serve as a monitor are not contained in the PPHS application, they must be added to the DSMP either as a narrative description or as a CV.

**MSSM Additional Monitor:**

Check One: PI:  Team Member:  Independent:

Last Name: [name]

First Name: [name]

Academic Title: Professor of Medicine

Department: Medicine

Mailing Address: MSSM, [name],

[name]

[contact]

[contact]

E-mail: [contact]

Drs. [name] and [name] will be responsible for data and safety monitoring for this study on a daily basis. [name] will perform an independent monitoring in our study every three months.

2. Justify your choice of principal monitor in terms of the assessed risk to the research subject‘s health and wellbeing. In high risk studies when the principal monitor is independent of the study staff, indicate the individual’s credentials, relationship to the PI, and the rationale for selection.

This is an open-label, low-risk dietary intervention involving adult subjects with peritoneal dialysis, in a single clinical site over a period of about 1 month, and with one research team. Therefore, an independent DSMB is not warranted. Drs. [name] and [name] will be evaluating each and all of these patients on a regular basis to determine any potential adverse events. [name] will monitor independently the study, and will start after the enrollment of the first five participants and every 3 months onwards.

3. List the specific items that will be monitored for safety (e.g., adverse events, subject compliance with the protocol, drop outs, etc.).

***Data monitoring***

*The following elements will be monitored:*

- *Is recruitment proceeding as expected?*
- *Do cohort characteristics match the exclusion/inclusion criteria*
- *Any deviations from protocol*
- *Comment on timeliness, accuracy and confidentiality of all information both in study documents and database*
- *Missing data points*
- *Dropout rates*

***Safety monitoring***

*The following elements will be monitored:*

- *Serious and unanticipated adverse events*
- *The totality of adverse events including expected and less than serious*
- *Reasons for subjects withdrawing from the study*
- *Changes in nutritional parameters from baseline*
- *Changes in concomitant medications*

4. Indicate the frequency at which **ACCUMULATED** safety and data information (items listed in number 3 above and interim analysis of efficacy outcomes) will be reviewed by the monitor(s) or the Data Monitoring Committee (DMC). Although this information must be reviewed at least annually, the higher the study risks, the more frequently reviews must be scheduled.

Monitoring will take place at every visit or following any serious adverse event until the completion of the study. Cumulative safety and data monitoring will be reviewed semiannually. Independent monitor will review cumulative data and safety semiannually.

Semiannually we will create a summary of safety to be reviewed by the Independent Monitor, [name], and to be sent to the MSSM IRB with an annual progress report.

5. Where applicable, describe rules which will guide interruption or alteration of the study design.

Participation of a person will be terminated in cases of noncompliance with study diet and design.The participation of candidates who fail to answer the follow up phone calls for 2 consecutive weeks, or report the nonadherence to diet for more than one week will be terminated.

6. Where applicable, indicate dose selection procedures that will be used to minimize toxicity.

N/A. This is a dietary intervention. No dose selection is possible.

7. List any specialized grading system that will be used to evaluate adverse events (e.g., National Cancer Institute Common Toxicity Criteria).

N/A.

8. Describe procedures that will be used to assure data accuracy and completeness.

This is a study involving a small number of subjects for about 1-month period by an experienced research team (Dr. [name], [name], [name], research coordinator(s) and study dietitian(s)), which will pay personal attention to each participant.

9. Should a temporary or permanent suspension of your study occur, in addition to the PPHS, to whom (NIH, FDA, sponsor, IRB) will you report the occurrence?

Any such situation will be immediately reported to the IRB, and PDU.

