**Step 3: Phone calls follow up: (15 minutes)**

The study team will contact both groups twice weekly and take a brief diet evaluation to assess the AGE content of their diet and compliance with the protocol.

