Withdrawal without subject’s consent: The study doctor, the sponsor or the institution may stop a subject’s involvement in this research study at any time without their consent. This may be because the research study is being stopped, the instructions of the study team have not been followed, the investigator believes it is in their best interest, or for any other reason. If specimens or data have been stored as part of the research study, they too can be destroyed without their consent.

1. Risks to Subjects

There are no known risks associated with low AGE diet. If participants are randomized to the high AGE diet (usual diet), they are not going to change their diet, and then the risks of maintaining that diet remain the same.

Qualified staff will draw blood using standard sterile equipment. Some people may experience a small amount of pain. On rare occasions, minor bruising may occur. These effects will self-resolve within hours or days. Occasionally, people feel faint or faint after blood draws.

Participants will be asked to bring a 24-hour urine and stool collection for 2 visits, which may create some inconvenience.

There are no risks associated with the AGE reader which only uses a light source to illuminate AGEs in the skin.

We cannot identify any physical or social risks for study participants.

There is a slight concern about possible lost of earnings during the study visit; however, the subject will determine and decide if participating in the study is more important/beneficial then earning wages.

There always exists the potential for loss of private information; however, there are procedures in place to minimize this risk.

1. Provisions for Research Related Injury

All subjects who will experience any side effect that is thought to be secondary to their participation in this study will be provided with all the medical or psychological resources they might need. Subjects with any kind of side effect should contact the study team.

1. Potential Benefits to Subjects

Participants are not expected to get any benefit from taking part in this research.  Although there is no direct benefit to participants in this study, we hope the results will help us to better understand the influence of dietary factors in the progression of the kidney disease. Therefore, we believe the risk/benefit ratio of this research favors the benefits.

1. Provisions to Protect the Privacy Interests of Subjects

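### Randomised participants can be terminated for non-adherence or missed calls before the only post-baseline samples, so the primary comparison can become one of selected completers

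*Protocol*

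**What the plan says.** Randomisation takes place at the first visit (Study Timelines, first visit). G1 stays on its usual diet and G2 moves to a low AGE diet. Step 3 then provides that "The study team will contact both groups twice weekly and take a brief diet evaluation", to assess AGE content and compliance.

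The termination rule is in the monitoring plan, Part I, item 5. The general sentence is "Participation of a person will be terminated in cases of noncompliance with study diet and design". Two specific triggers follow. One covers those who "fail to answer the follow up phone calls for 2 consecutive weeks". The other covers those who "report the nonadherence to diet for more than one week will be terminated".

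Withdrawal of Subjects separately lets the team remove a participant without consent when study instructions were not followed. It adds: "If specimens or data have been stored as part of the research study, they too can be destroyed without their consent".

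Step 4 places the final stool, blood, urine and skin measurements one month after the first visit. Study Endpoints names change in gut microbiota as the primary endpoint. Number of Subjects expects 20% dropout and says that 15 per group "will be sufficient to achieve at least 10 participants in each group at study end".

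**The concern.** The rule removes people for something they do after randomisation, and it can do so before the primary outcome is measured. The outcome is a change, so someone without a final stool sample contributes nothing to it. Those who remain are selected on adherence and on responsiveness to calls, and both may be related to the outcome.

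The two groups are not asked for the same thing. Entry requires a high habitual AGE intake. G2 must give that diet up, while G1 only has to carry on, so a rule about adherence to diet probably falls more heavily on G2. If so, part of any difference in microbiota or inflammatory markers could reflect who stayed rather than what they ate.

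This is not a matter that can wait for a statistical analysis plan. Such a plan can define analysis sets, but it cannot analyse samples that were never collected.

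**Working it through.** **1. Timing.** Calls start after randomisation. More than one week of reported non-adherence can be reached at about day 8, and two weeks of unanswered calls at about day 14. The only outcome samples are at about one month, so both triggers can act first. No section keeps terminated participants in follow-up or asks them for final samples.

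**2. The plan's own figure.** With 15 per group and 20% dropout, 15 × 0.8 = 12 are expected to complete, which meets the target of at least 10. With binomial completion at 0.8, the chance of at least 10 of 15 is 0.939 in one group and 0.939² = 0.88 in both. The enrolment arithmetic holds. The Protocol does not say whether the 20% includes enforced terminations, and does not split it by group.

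**3. Effect on numbers if terminations come on top of the 20% and fall on G2** (extra shares assumed; G1 stays at 20%):

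| Extra share of G2 removed | Expected G2 completers | Chance of at least 10 in both groups |
|---|---|---|
| 0% | 12.0 | 88% |
| 10% | 10.8 | 73% |
| 20% | 9.6 | 50% |
| 30% | 8.4 | 27% |

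**4. Selection bias, illustration.** Assumptions, none of them in the Protocol: no true diet effect, the least adherent fraction q of G2 removed, nobody removed from G1, and correlation ρ between adherence and outcome. The shift in the completer contrast, in SD units, is ρ·φ(z_q)/(1−q), where φ is the standard normal density and z_q its q-quantile.

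- q = 0.20: φ(−0.842) = 0.280 and 0.280/0.80 = 0.350. The shift is 0.105 at ρ = 0.3 and 0.175 at ρ = 0.5.
- q = 1/3: φ(−0.431) = 0.364 and 0.364/0.667 = 0.545. The shift is 0.164 at ρ = 0.3 and 0.273 at ρ = 0.5.

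Simulation of a two-sided 5% t-test, starting from 15 per group, rejects in about 5.8% to 7% of trials at q = 0.20 and about 6.5% to 10% at q = 1/3.

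**5. Sensitivity to those assumptions.**

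- 20% removed from G2 and 2 of 15 from G1 under the same selection: the G1 factor is 0.248, so the shift is ρ × (0.350 − 0.248), or 0.03 at ρ = 0.3 and 0.05 at ρ = 0.5. Rejection is about 5% to 6%.
- Equal removal in both groups: bias is about zero and rejection is close to 5%.
- G2-only removal with ρ = 0.1: the shift is 0.035 (q = 0.20) to 0.055 (q = 1/3), and rejection is about 5%.

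For scale, the standard error of the contrast is √(1/15 + 1/12) = 0.39 SD with 12 left in G2, and √(1/15 + 1/10) = 0.41 SD with 10 left.

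**The case against.** A reader might infer that the Protocol builds in attrition that differs by arm. It does not say so. It gives one dropout rate for both groups, and the missed-call rule covers both. G1 also receives AGE education and handouts, so a G1 participant could leave the usual diet and meet the adherence trigger. Higher loss in G2 is a reasonable expectation from the design, not a documented fact.

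A reader might also infer that a third of each group is expected to go. Ten per group is the floor that the Protocol accepts; its expected rate is 20%. Nor does the Protocol say outright that final samples are refused. It says participation ends, and a trigger met late in the month need not precede the visit. Destruction of stored material is permitted, not required, and nothing shows that it is planned for non-adherers.

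The bias figures are one-sided. They assume loss in G2 only and strict selection on adherence. Because the endpoint is a change from baseline, stable differences between people partly cancel, which argues for a smaller correlation. Even the larger values are below one standard error. One can also argue that a mechanistic pilot cares most about people who followed the diet, and dropout is monitored throughout.

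All of this limits how strongly the size can be stated. It does not answer the main point. Monitoring makes losses visible but does not recover samples. An adherent-only analysis remains available if everyone is sampled, whereas an as-randomised analysis is not available if they are not.

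**Conclusion.** The point stands as a gap in outcome collection. Followed as written, the plan ends participation because of behaviour after randomisation, potentially before the only outcome measurement, and gives no route to the missing samples. The primary comparison can then be one of selected completers.

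The direction and size of any bias are not established. About 0.1-0.27 SD, with 6-10% rejection at a nominal 5%, applies only if removals fall on the least adherent 20-33% of G2 alone and adherence correlates 0.3-0.5 with the outcome. If G1 loses people similarly, or the correlation is near 0.1, bias is close to zero and rejection close to 5%. The Protocol does not support a claim that attrition will differ by arm, only that this is likely. The gap still needs closing before enrolment, because samples not taken cannot be recovered.

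**What to change.** Separate adherence from follow-up. In Part I, item 5, replace the termination sentences with:

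> Non-adherence and missed calls will be recorded. All randomised participants will be asked to attend the one-month visit and give all samples unless they withdraw consent.

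Align Withdrawal of Subjects, which would otherwise contradict this wording. Not following study diet or call instructions should neither end outcome collection nor lead to destruction of samples or data already collected. Leave removal in the participant's interest or on closure of the study as it is.

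Compare all randomised participants who have samples in their assigned groups, with an adherent-only analysis as supportive.

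The cost is mainly wording. The final visit already coincides with the routine monthly dialysis visit, so little extra effort is needed. The downside is that non-adherers dilute the as-randomised effect. In return the pilot gains usable data on adherence and retention.
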